**I. Aims of the Study:**

The overall aim of the study concerns the development and evaluation of an integrated approach that combines (a) mental health treatment with (b) an empowerment intervention, to reduce psychological distress and intimate partner violence against female refugees from the Democratic Republic of the Congo (DRC) in Tanzania.

Specifically, the study aims to:

1. Pilot measurement tools assessing identified priority mental health conditions, functional impairment and intimate partner violence in Nyarugusu refugee camp.
2. Develop and pilot implementation of the proposed integrated intervention combining and adapting elements of cognitive processing therapy (CPT) and empowerment counseling.
3. Conduct a randomized controlled trial of the intervention, to examine if the collaboratively developed intervention is associated with reductions in prioritized mental health problems and intimate partner violence, compared to a set of currently existing standard operating procedures
4. Conduct a qualitative process evaluation to examine facilitators and barriers to implementation of the research and intervention protocols in Nyarugusu refugee camp.

***Preliminary aims of this study (not described above) included conducting a qualitative study to identify and characterize priority mental health problems and health seeking behavior. The JHSPH IRB determined these preliminary aims to not be human subjects research as defined by DHHS regulations 45 CFR 46.102 and thus did not require IRB oversight (IRB #5706, FWA #00000287, Nov. 11, 2014)***

**II. Background and Rationale:**

The proposed research directly targets two public health areas with major gaps in evidence in the field of humanitarian settings: (1) gender-based violence and; (2) mental and psychosocial health.

**Gender-based violence**: With regard to gender-based violence in refugee settings specifically, Asgary and colleagues (2013) conducted a wide and inclusive systematic review, but did not identify any studies that evaluated prevention and reduction of GBV in this population. We therefore discuss evidence from non-humanitarian contexts and non-refugee populations, focusing on intimate partner violence as a subset within the broad category of gender-based violence. Systematic reviews have focused on two types of interventions to reduce intimate partner violence in health-care settings: (1) universal screening and (2) empowerment (advocacy)-focused counseling.

***Universal screening*** has been a contested practice (Jewkes 2013). Recent systematic reviews have found that although five screeners have shown diagnostic accuracy to detect IPV (Nelson et al. 2012), universal screening itself does not seem to be associated with a reduction in IPV rates or improved health outcomes (5 trials of low-moderate quality) (Taft et al. 2013; World Health Organization 2013b). Since effective interventions exist to target intimate partner violence, the US Preventive Services Task Force recommends universal screening of women of reproductive age and linking them with services (Moyer 2013), whereas the WHO (2013b) only recommends screening of women who show signs or symptoms of intimate partner violence.

With regard to ***empowerment counseling***, a WHO review (2013b) identified 15 studies that examined a heterogonous mix of components including: linking women to services, empowering women, and promoting safety behaviors. Findings showed that these interventions may reduce intimate partner violence in some women, but there are gaps in knowledge with regard to: if intimate partner violence interventions alone may improve mental health and quality of life outcomes; whether intimate partner violence interventions are effective when implemented with women outside of shelters/ safe houses; and if the positive results with women in antenatal clinics can be generalized to other settings. These findings are similar to findings from a Cochrane review on effectiveness of advocacy interventions to reduce IPV (Ramsay et al. 2009).

**Mental health:** A systematic review on mental health and psychosocial support interventions in humanitarian settings ([name] et al. 2011) concluded that there is moderate level evidence that more specialized treatments can reduce posttraumatic stress disorder (PTSD) in humanitarian settings (meta-analysis of 9 treatments, low statistical heterogeneity), but uncertainty with regard to other outcomes and approaches. None of the studies identified in this systematic review were conducted specifically with populations exposed to intimate partner violence. Later systematic reviews that specifically searched for evidence for interventions for sexual and gender-based violence in conflict-affected populations ([name] et al. 2013b) and refugee populations (Asgary et al. 2013) confirm this lack of studies.

However, a randomized controlled trial published by Bass and colleagues in 2013 has shown that group Cognitive Processing Therapy was associated with strong reductions in symptoms of common mental disorders (anxiety/ depression) and posttraumatic stress disorder (PTSD), as well as functional impairment among gender-based violence survivors (Bass et al. 2013). Furthermore, we may build on evidence of mental health interventions for trauma-affected populations more broadly. This evidence was reviewed by the PI as part of the development of WHO recommendations on how to manage stress-related conditions and disorders (acute stress, PTSD, bereavement) in non-specialized health care settings in low- and middle-income countries ([name] et al. 2013a; World Health Organization 2013a). With regard to PTSD, these guidelines recommend individual cognitive behavioral therapy with a trauma focus (CBT-T) and eye movement desensitization reprocessing (moderate level evidence), as well as group CBT-T and stress management (low level evidence).

Mental health and intimate partner violence are inter-related. Intimate partner violence is a known risk factor for a range of mental health conditions including PTSD, depression, anxiety, substance use, and suicidal behaviors (Howard et al. 2013; [name] et al. 2011). Mental health problems in turn, put women at a higher risk for further gender-based violence. Combining these interrelated risk factors for wellbeing may produce synergistic effects. For example, women with improved mental health may be in a better position to negotiate safety and their right to be protected from violence. Vice versa, empowerment and reductions in violence may contribute to improved mental health. Against this background, the overall aim of this study is to test an integrated intervention model that addresses both sides of this vicious cycle. We will build on the study conducted by Bass et al. with women residing in the DRC to develop and test an abbreviated evidence-based mental health intervention combined with empowerment in refugees from the DRC in Tanzania.

**III. Study Design**

1. Provide an overview of your study design and methods. The study design must relate to your stated aims/objectives. Details will be requested later. If your study also involves analysis of existing data, please complete Section XI, “Secondary Data Analysis of Existing Data” in the last part of this research plan. If your study ONLY involves analysis of existing data, please use the research plan template for secondary data analysis (JHSPH IRB Research Plan for Secondary Data Analysis of Existing Data/Specimens).

AIM 1: Pilot measurement tools assessing identified priority mental health conditions, functional impairment and intimate partner violence in Nyarugusu refugee camp

We have selected measurement tools that have been used in previous research on mental health and IPV and were consistent with the priority mental health and psychosocial problems affecting female survivors of IPV in Nyarugusu identified in our previous qualitative research (please see section V.B.4 and attached measures). However, because these tools have not been validated in Congolese refugees residing in Nyarugusu refugee camp, we plan to conduct a validation study prior to starting the randomized controlled trial. For the validation study we will recruit 60 women from zone 1 meeting the eligibility criteria for the trial to complete the screening and baseline assessment and participate in the intervention during the pilot period. The measurement validation and pilot intervention activities will be implemented by the research staff and intervention facilitators hired to complete the randomized controlled trial. For purposes of measurement validation, we will not conduct the post-intervention assessment with the pilot participants because there are no new measures introduced during these assessments. Thus, completing the screening and baseline assessments during the pilot phase will be sufficient for completing our objective of evaluating the validity and reliability of these measurement tools among women in Nyarugusu. Using pilot measurement validation data we will be able to assess inter-rater reliability, internal consistency, construct validity, test-retest reliability and face/content validity as follows.

1. *Inter-rater reliability* will be assessed by having all research assistants observe and document the same three screening and baseline pilot interviews and having one member of the research team role play as a participant. Inter-rater reliability will then be quantified by the intraclass correlation coefficient (ICC 3,10) for all measures included in the assessments. This data has already been completed as part of the role-plays conducted during training, but the intraclass correlation coefficient has not yet been calculated.
2. *Test-retest reliability* will be assessed by having the first 24 pilot participants complete the screening and baseline assessments twice (one week apart, administered by the same research assistant) prior to commencing the pilot intervention. The correlation of a given measure between these two assessments will be calculated to determine test-retest reliability. This will be evaluated once all pilot assessments have been completed.
3. *Internal consistency* will be assessed by calculating Cronbach’s alpha for each measure as well as evaluating whether the reliability substantially improves upon removal of any single item. We will also calculate item-rest correlation to assess the correlation between a single item and the total scale score (excluding the item under study). Internal consistency will be evaluated once all pilot assessments have been completed.
4. *Construct validity* will be assessed by evaluating both internal convergent and discriminant validity. To evaluate construct validity we will compare the correlation of scores on the Abuse Assessment Screen, the Demographic and Health Survey Domestic Violence Module, the Hopkins Symptom Checklist, the Harvard Trauma Questionnaire and other measures included in the screening and baseline assessment. We expect measures assessing the same construct (e.g. IPV), but on different measures will be more highly correlated (convergent validity) than that of measures assessing different constructs (discriminant validity). Using the correlations between these constructs and measures we will develop a multi-trait, multi-method matrix that will allow us to compare the relative magnitude of reliability, convergent validity and discriminant validity correlation coefficients. We hypothesize that the reliability coefficients will be highest followed by convergent validity, which will be larger than the discriminant validity coefficients. Construct validity will be evaluated once all pilot assessments have been completed.
5. *Face and content validity* has been assessed by the research team and healthcare workers in Nyarugusu during the training process. Face and content validity describe the extent to which items included in a measure appear relevant to the construct of interest (face validity) and whether they cover the entire domain of that construct (content validity). During the training and measurement development process, the research team thoroughly reviewed each measure and discussed what was intended by each item and how it relates to the construct of interest. Measures that were not relevant to the setting in Nyarugusu were removed or adapted as needed. Furthermore, clinicians and public health professionals with experience in mental health also reviewed the measures to evaluate face and content validity. Upon completion of the pilot assessment, the measures will again be reviewed by the research team and public mental health experts to evaluate face and content validity.

AIM 2: Develop and pilot implementation of the proposed integrated intervention combining and adapting elements of cognitive processing therapy (CPT) and empowerment counseling.

The 60 women that complete the pilot screening and baseline assessment will then enter into a pilot intervention cohort. The pilot intervention will resemble the intervention procedures (described in section V.C.2 Intervention Study Visits). The intervention will begin with an individual empowerment counseling session with one of the intervention facilitators followed by seven sessions (1 per week) of group integrated cognitive processing therapy and empowerment counseling. The purpose of the pilot intervention phase is to assess implementation of the intervention, as opposed to an outcome evaluation. A psychiatrist and/or psychologist from Muhimbili University of Health and Allied Sciences (MUHAS) that has been trained in the intervention will observe intervention sessions and provide feedback to the intervention facilitators throughout the study period. Participant safety protocols (e.g. suicide risk assessments, etc.) will be in effect throughout the pilot period as they would during the randomized controlled trial (see section V.B.6.f). There will be no control group enrolled during the pilot period. The pilot period has not yet started.

AIM 3: Conduct a randomized controlled trial of the intervention, to examine if the collaboratively developed intervention is associated with reductions in prioritized mental health problems and intimate partner violence, compared to a set of currently existing standard operating procedures

We plan to conduct a cluster randomized controlled trial evaluating the efficacy of the aforementioned integrated mental health treatment and intimate partner violence prevention intervention as compared with a treatment as usual control group. In Nyarugusu Refugee Camp, the setting of this study, there are 7 zones within which refugees live. These zones are further subdivided into 52 villages. Women’s groups (described in further detail below; section IV. Participants) operate within these villages and will serve as the site of recruitment and the unit of randomization. Women entering the trial will be assessed for symptoms of mental health problems, intimate partner violence and other related constructs at baseline (week 1) and one post-intervention follow-up at week 10. All measurement and data collection is based on self-report indicators reported by the participant. The intervention is designed to last approximately 2 months (8 sessions, once per week for 8 weeks) with full participation in the study lasting 10 weeks (baseline to follow-up).

AIM 4: Conduct a qualitative process evaluation to examine facilitators and barriers to implementation of the research and intervention protocols.

We plan to conduct a qualitative process evaluation of the implementation of the Nguvu intervention and research protocols within the context of the randomized controlled trial described in Aim 3. To do so we will recruit a subset of participants (n=10), both high (n=5) and low attenders (n=5) from the intervention condition to participate in a qualitative interview with a member of the research team to discuss their experience participating in the intervention related to perceived challenges, risks, benefits, operations and acceptability. We will also qualitatively interview the 10 intervention facilitators and their clinical supervisor to identify their perspectives on successes and challenges of the intervention as well as their experiences as a provider of these services. Lastly, we will conduct qualitative interviews with seven representatives from partner agencies and the community advisory board to examine structural challenges to implementation as well as the perceived impact that implementing Nguvu had at the community and organizational level. We estimate that each of these interviews will take approximately one hour to complete and will be delivered by our trained research assistant team.

1. Provide a sample size and a justification as to how you arrived at that number. If you use screening procedures to arrive at a final sample a table may be helpful.

Pilot Study:

We have chosen to include 60 women in the measurement validation and pilot intervention phase because this sample size will allow for each pair of facilitators (5 pairs in total) to run through the entire intervention starting with 12 women each. Sixty participants is also a sufficient sample size to meet the objectives of our measurement validation activities.

Randomized Controlled Trial:

Our primary outcomes are both assessed on a continuous scale, thus we conducted a sample size calculation for the randomized controlled trial intended for two-sample mean comparisons using one of our primary outcomes of interest, psychological distress. We gathered information from previous trials measuring our primary outcome(s) of interest in similar populations to estimate the following parameters used for the sample size calculation:

$$\sigma_{time1}^{2}=0.25$$

$$\sigma_{time2}^{2}=0.36$$

$$\rho=0.333$$

$$\sigma_{change}^{2}=0.55007$$

$$m=10$$

$$\mu_{1}=1.3$$

$$\mu_{2}=0.7$$

$$N=\frac{2\left( z_{\frac{\alpha}{2}}+z_{\beta} \right)^{2}(\sigma^{2})(1+\left( m-1 \right)\rho)}{{(\mu_{1}-\mu_{2})}^{2}}=\frac{2\left( 1.96+0.842 \right)^{2}(0.55007)(1+\left( 18.269-1 \right)0.333)}{{(1.3-0.7)}^{2}}=161.97$$

In order to have 80% power to detect a treatment effect of similar magnitude as previous trials that are roughly comparable in terms of intervention and population at the 0.05 significance level, we need 162 persons per group. To account for 10% attrition, we will recruit a target sample of 180 participants per group (360 total).

Process Evaluation:

We will conduct a total of 28 qualitative interviews as part of the process evaluation. We will recruit a subset of the participants that were enrolled in the randomized controlled trial (n=10) to participate in the process evaluation. We will recruit 10 intervention facilitators, their clinical supervisor (n=1) and 7 members of local partner organization to interview regarding implementation facilitators and challenges. These new participants will not be interviewed regarding personal health information and the focus of the interviews will be on program implementation.

Total Sample Size:

The total number of participants that will be enrolled in the pilot study and randomized controlled trial is 420 (60 in pilot, 360 in trial). We will recruit an additional 18 personnel who have not participated as a client in Nguvu to qualitatively interview regarding the implementation of the research and intervention protocols.

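### Inter-rater reliability rests on three training role-plays acted by a team member, so it shows recording agreement only and cannot support the Aim 1 claim of reliability among women in Nyarugusu

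*Protocol*

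**What the plan says.** Protocol section III, AIM 1, explains that the tools have not been validated in this population. It says screening and baseline interviews with 60 pilot women will suffice for "evaluating the validity and reliability of these measurement tools among women in Nyarugusu", and lists inter-rater reliability first among the properties to be assessed from the pilot data.

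Item 1 then defines the inter-rater exercise, in which every assistant takes part, in these words: "observe and document the same three screening and baseline pilot interviews and having one member of the research team role play as a participant". On the source it adds: "This data has already been completed as part of the role-plays conducted during training". The summary is fixed too: "Inter-rater reliability will then be quantified by the intraclass correlation coefficient (ICC 3,10) for all measures included in the assessments". No value is given, because the coefficient had not been calculated.

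Under AIM 2 the protocol states: "The pilot period has not yet started". Under AIM 3 it states: "All measurement and data collection is based on self-report indicators reported by the participant". Section V.A gives the number of research assistants as ten. Section V.C describes a research assistant conducting each woman's baseline interview, and describes the symptom checklists as administered by interview.

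**The concern.** The announced source (pilot participants) and the actual source (training role-plays) do not match, and the role-plays cannot deliver the property that Aim 1 names. There are three reasons.

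- **Error source.** All assistants document the same administration. Any effect of how a question is put, probed or received is shared by all ten records and drops out of the comparison. What is left is recording and scoring error. In the trial, an assistant's own interviewing also shapes the score, on questions about violence and distress that a woman may or may not choose to disclose.
- **Between-subject variance.** An intraclass correlation is a share of variance. Here its numerator is the spread that was acted, not the spread among women in the camp.
- **Number of targets.** Three interviews leave 2 degrees of freedom between subjects.

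At stake is whether Aim 1 may conclude that the tools are reliable between assistants in this population. If assistants do elicit different scores, this exercise would not show it.

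**Working it through.** There is no figure of the plan's own to reproduce.

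**1. Were any real participants rated?** Read alone, item 1 could mean three real pilot interviews plus one role-play. But the data are said to be complete already, from training role-plays, and AIM 2 says the pilot had not started. So no pilot woman contributed.

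**2. Does another Aim 1 analysis contrast interviewers?** Test-retest uses the first 24 pilot women, one week apart, with the same assistant both times. Internal consistency and construct validity do not separate interviewers. So none does.

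**3. Precision with three targets.** Inputs: n = 3 interviews (III, AIM 1, item 1) and k = 10 assistants (V.A). Degrees of freedom: n − 1 = 2 and (n − 1)(k − 1) = 18. The 97.5% points are F(2,18) = 4.56 and F(18,2) = 39.44.

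- Formula: F = [1 + (k − 1)r]/(1 − r). Put F_L = F/4.56 and F_U = F × 39.44. The single-rater limits are (F_L − 1)/(F_L + 9) and (F_U − 1)/(F_U + 9).
- Observed r = 0.80: F = (1 + 9 × 0.80)/0.20 = 41, F_L = 8.99, F_U = 1617. The limits are 7.99/17.99 = 0.44 and 1616/1626 = 0.99.
- Observed r = 0.70: F = 7.3/0.3 = 24.3. The limits are 0.30 and 0.99.
- The same F = 41 in the planned ten-rater form gives 1 − 1/41 = 0.976, with limits 1 − 1/8.99 = 0.89 and 1 − 1/1617 = 0.999.

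**4. Can the design see elicitation error?** This is an illustration on assumed values: true-score variance 0.25 (the section III time-1 variance, treated here as true-score variance), recording SD 0.05 (variance 0.0025), and administration SD a from 0 to 0.35.

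- Shared administration: (0.25 + a²)/(0.25 + a² + 0.0025)
- Each assistant interviews: 0.25/(0.25 + a² + 0.0025)

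| a | Shared | Own interview |
| --- | --- | --- |
| 0 | 0.99 | 0.99 |
| 0.15 | 0.99 | 0.91 |
| 0.25 | 0.99 | 0.79 |
| 0.35 | 0.99 | 0.67 |

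The planned design returns about 0.99 whatever the elicitation error. The size of a in Nyarugusu is unknown; the table shows only that the design is blind to it.

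**5. Dependence on acted spread.** With an assumed rater error variance E = 0.10, V/(V + E) is 0.25/0.35 = 0.71 at V = 0.25. It is 1.0/1.1 = 0.91 if the three role-plays score 1, 2 and 3 (variance 1.0). With E = 0.05 the pair is 0.83 and 0.95; with E = 0.15 it is 0.625 and 0.87. If the protocol's 0.25 already includes measurement error, the first figure becomes (0.25 − 0.10)/0.25 = 0.60.

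**The case against.** Having several raters score the same material is the ordinary meaning of inter-rater reliability, and recording and scoring agreement is a genuine part of interviewer error. Consent and screening are one-to-one and private, and disclosure carries safety risks, so ten observers at a survivor's interview would be hard to defend. Role-play is a reasonable training exercise. All of this stands. The complaint is about what the result is said to show, not about having done the exercise.

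The error variances in the illustrations are assumed, and the planned ten-rater coefficient would look far tighter (0.89 to 0.999) than the single-rater one. That also stands. But the ten-rater form describes the mean of ten assistants, whereas section V.C has an assistant conducting each interview. A narrow interval also does not remedy the acted spread or the missing elicitation component.

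A reader might go further and infer that the primary analysis is compromised or the treatment effect biased. The protocol does not support this. The coefficient enters neither the sample size nor any decision rule, assessors are to be blind to assignment, and visits follow the same process in both arms. Interviewer differences would mainly add noise. Nor does the absence of an interviewer term in the primary model count as a fault; that is an analyst's choice. A reader might also take the answers to have been scripted, but the text says only that they were role-played.

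**Conclusion.** The point holds in a limited form. Aim 1 promises inter-rater reliability from pilot data for tools used with women in Nyarugusu. What it has is recording and scoring agreement on three acted interviews, collected before any pilot woman was seen. That cannot support the stated property, and no other Aim 1 analysis supplies it.

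The precision result, 0.44 to 0.99 around a single-rater value of 0.80, depends on the protocol's three interviews and ten assistants and on the usual F-based interval; the 0.80 itself is hypothetical. The effects of acted spread and hidden elicitation error are shown over assumed ranges and do not estimate their size in this camp. The consequence stops at the Aim 1 reliability claim.

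**What to change.** - In Protocol section III, AIM 1 (opening text and item 1), describe the role-play result as recording agreement from training. Report percent agreement and the within-interview rater SD, or a single-rater intraclass correlation, with a confidence interval. Do not present it as reliability in Nyarugusu women.
- Record the interviewing assistant's ID on every form. The quality check in section V.C asks for the assistant's name, but reaches only a random 10% of participants and depends on their recall.
- For each scale, report the between-interviewer share of variance from the 60 pilot interviews and again from the 360 trial baselines, adjusted for women's group where possible.

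The cost is some rewording, one field per form and a short analysis of interviews already planned; no extra interviews are needed. The downside should be stated with the result. The pilot estimate is imprecise, at 60/10 = about 6 women per assistant. Either estimate may mix interviewer effects with real differences between women, because the protocol does not say that assistants are assigned at random.
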